#### RCT secondary analyses

We will compare CRC screening coverage between the two groups using the Wilcoxon rank sum test. Additionally, we will calculate descriptive summaries (mean, standard deviation, median, and range) for the entire sample and by group.

#### RCT sample size and power

Based on our prior studies (33–37), we anticipate CRC screening rates will be between 5 and 12% in usual care and 10–35% in the mPATH^®^-CRC arm, with at least a 5–7% absolute difference between arms, conservatively. With *n* = 500 in each arm, we will have more than 80% power to detect such differences (5–7%) between the arms at 1-sided alpha level 0.05.

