mPATH^®^CRC was designed to “identify patients due for CRC screening, educate them on the commonly used screening tests, and help them select their best option, with the goal of increasing CRC screening rates” [15]. Thus far, mPATH^®^-CRC has been used in primary care clinics wherein patients use an iPad during check-in to view a decision aid about CRC screening options and answer questions about their screening preferences [15]. In a randomized controlled trial conducted in primary care practices affiliated with a large academic health system, an iPad version of mPATH^®^-CRC doubled the proportion of patients who completed CRC screening compared to usual care (30% versus 15%) [16]. However, while this study found mPATH^®^CRC to be effective as a clinical in-reach strategy (i.e., used for patients with appointments), less is known about factors effecting implementation and effectiveness of this type of technological solution with lower-resourced FQHCs that serve patients with relatively lower socioeconomic status. Particularly, delivery during appointments is challenging for FQHCs that have limited staff time and patients with less consistent appointment routines.

This study will implement mPATH^®^CRC with FQHCs using a novel outreach strategy that identifies patients and delivers intervention components to patients outside of regular appointments. This outreach strategy could increase reach and mitigate implementation barriers. The effectiveness will be evaluated using a pragmatic randomized controlled trial designed and anchored in the Process Redesign Framework for understanding both effectiveness and implementation in resource-constrained settings.

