### RCT sampling and procedures

Figure 1 provides the study flow. A more detailed study schema is found in the Supplementary Materials. The FQHC will send an EHR query of all eligible (active) patients from their clinic sites approximately once per week to the research team (this list will be updated regularly to include newly added patients and remove previously selected patients or those who become current with screening). A biostatistician on our research team will use a computer-generated random sequence to select patients from the list within strata of appointment status and race/ethnicity: equal patients with an upcoming clinical appointment within approximately 21–45 days and patients without an upcoming clinical appointment (or an appointment greater than 45 days), and within each appointment status strata, equal patients from each of the four race/ethnicity groups represented in the FQHC’s patient population (White, Africa American, Hispanic, and American Indian). Next, we will randomize 1:1 to the mPATH^®^-CRC intervention and usual care within each appointment status and race stratum. We will repeat these sampling procedures until we reach our target sample of 1000 total patients after 8 months. We will follow this cohort for three total years, repeating the same outreach each year dependent on screening modality and completion (i.e., completion of colonoscopy in year 1 would no longer require follow-up, completion of FIT would require annual testing).

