### Analyses

#### RCT primary outcome analyses

For the RCT design, our main statistical test for the primary outcome (CRC screening completion) will be a Mantel-Haenszel chi squared test, adjusted for stratification factors (appointment status, race/ethnicity), following the intention to treat principle. If there are differences between the arms across baseline variables known to be associated with the outcome, we will use multiple logistic regression, adjusting for the variables. Specifically, due to the potential for differential response, sex will be included in all analyses as a biologic variable. One-sided tests will be used because we expect active intervention will lead to more favorable results compared to usual care. Under the intention to treat principle, our primary analysis will be a crude comparison of proportions of completed CRC screening at six months between the mPATH^®^-CRC and usual care arm using a one-sided Mantel-Haenszel chi-squared test, controlling for stratification factors (appointment status and race/ethnicity), conducted at the 0.05 significance level. As a minimal risk study using only strategies known to improve evidence-based screening, we will not convene a formal data monitoring committee.

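### The claim of more than 80% power fails for a 5-point difference once usual-care screening exceeds about 8.9%, although the plan anticipates up to 12%

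*Protocol article*

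**What the plan says.** Under RCT sample size and power, the protocol article gives two ranges of rates: "we anticipate CRC screening rates will be between 5 and 12% in usual care", and "10–35% in the mPATH^®^-CRC arm". It adds a range of differences, "with at least a 5–7% absolute difference between arms, conservatively". One power statement then covers them all for 500 patients per arm: "we will have more than 80% power to detect such differences (5–7%) between the arms at 1-sided alpha level 0.05".

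The RCT primary outcome analyses section is consistent with this. The primary test is a one-sided Mantel-Haenszel chi-squared test, "controlling for stratification factors (appointment status and race/ethnicity), conducted at the 0.05 significance level". Allocation is 1:1 with a target of 1000 patients. The outcome is taken from the health record for everyone randomized, and no allowance for dropout is built into the figure of 500.

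**The concern.** With a fixed number per arm and a fixed absolute difference, power falls as the usual-care rate rises towards 50%, because the binomial variance grows. A single power figure covering usual care from 5 to 12% therefore has to hold at 12%, and one covering differences of 5 to 7 points has to hold at 5 points. The combination that tests the claim hardest is 12% versus 17%, and the text does not exclude it.

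This is the only justification given for the sample size on the primary outcome. If usual care turned out at 10 to 12% and the result were null, a reader relying on the stated power would put the chance of having missed a true 5-point gain below 20%. The calculation puts it at about 23% (10% usual care) to 27% (12%).

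**Working it through.** **Inputs, all from the protocol article.** n = 500 per arm; one-sided alpha 0.05, so z = 1.645; usual-care rate p1 from 5 to 12%; difference d of 5, 6 or 7 points, with p2 = p1 + d; no dropout.

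**Formula.** Two proportions, pooled variance under the null and unpooled under the alternative, with p̄ = (p1 + p2)/2:

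- SE0 = √[2 p̄(1 − p̄)/n]
- SE1 = √[(p1(1 − p1) + p2(1 − p2))/n]
- Power = Φ[(d − 1.645 × SE0)/SE1]

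**Where the plan's figure is reproduced.**

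- 5% v 10%: SE0 = √(0.13875/500) = 0.01666; SE1 = √(0.1375/500) = 0.01658; (0.05 − 0.02740)/0.01658 = 1.363; power 91.4%.
- 12% v 19%: SE0 = √(0.26195/500) = 0.02289; SE1 = √(0.2595/500) = 0.02278; (0.07 − 0.03765)/0.02278 = 1.420; power 92.2%.

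**Where it is not.**

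- 10% v 15%: SE0 = √(0.21875/500) = 0.02092; SE1 = √(0.2175/500) = 0.02086; (0.05 − 0.03441)/0.02086 = 0.748; power 77.3%.
- 12% v 17%: SE0 = √(0.24795/500) = 0.02227; SE1 = √(0.2467/500) = 0.02221; (0.05 − 0.03663)/0.02221 = 0.602; power 72.6%.

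**Over the plan's range.**

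| Usual care | 5 points | 6 points | 7 points |
|---|---|---|---|
| 5% | 91.4% | 96.9% | 99.0% |
| 7% | 85.4% | 93.6% | 97.6% |
| 8% | 82.6% | 91.8% | 96.7% |
| 9% | 79.8% | 90.0% | 95.7% |
| 10% | 77.3% | 88.1% | 94.6% |
| 11% | 74.9% | 86.3% | 93.4% |
| 12% | 72.6% | 84.5% | 92.2% |

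Solving for the usual-care rate at which 5-point power equals 80% gives 8.9%. At 12% usual care, the difference with 80% power is 5.6 points. Reaching 80% power for 12% v 17% would take 613 per arm.

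**Does the choice of method matter?** The 80% crossing for 5 points is 9.0% with unpooled variance, 9.1% with the arcsine method and 7.9% with a continuity correction. Exact binomial enumeration of the pooled z-test gives 72.8% for 12% v 17% and 77.6% for 10% v 15%. At 9% v 14% the exact figure is 80.1% against 79.8% pooled, so 9% is borderline. Two-sided testing would be worse (61.3% for 12% v 17%).

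**Does stratification help?** The design has 2 appointment groups × 4 race/ethnicity groups = 8 strata. The one-sided Mantel-Haenszel test was simulated 200,000 times per setting with a 5-point difference in every stratum and 62 patients per arm per stratum (496 per arm, since 500/8 is not whole). Power was 72.7% with 12% usual care in every stratum. It was 73.5% with usual-care rates of 5, 6, 7, 8, 16, 17, 18 and 19%, which average 12%. Stratification adds about one point at most here.

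**The case against.** The strongest defence is that the two ranges were meant to move together, with 5 points going with 5% usual care and 7 points with 12%. The low ends fit: 5% in usual care and 10% in the intervention arm are exactly 5 points apart. On that reading power is 91% at one end and 92% at the other, and the statement is true. A condensed article could also leave the pairs of rates to the full protocol. This reading is coherent and may be what was intended. However, the article does not state the pairing. It gives a usual-care range, a difference range and one unqualified power figure for all the differences. A paired calculation would also have supported a claim of more than 90%. The point is not that detail is missing but that the sentence, as printed, is untrue for part of the range it covers.

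A second objection is proportion. The shortfall is confined to differences near 5 points with usual care above about 8.9%, and most of the claim holds. That stands. Design, test and significance level are unaffected, and a careful reader of a null result would look at the confidence interval before the planned power.

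A reader might also infer that the 5 to 12% range is itself too low. The Background reports 15% in usual care in an earlier trial among patients with appointments, and half of this sample is selected to have one: "equal patients with an upcoming clinical appointment within approximately 21–45 days and patients without an upcoming clinical appointment". The documents do not support that step. The earlier trial ran in practices of a large academic health system, which the Background itself contrasts with lower-resourced health centers. The other half of this sample has no appointment within 45 days. The 5 to 12% range is attributed to prior studies that are not available here. Purely as an illustration, 15% in the appointment half and an assumed 5% in the other half would average (15 + 5)/2 = 10%, inside the stated range.

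**Conclusion.** The power statement is correct for 6 and 7 points at every usual-care rate from 5 to 12%, and for 5 points up to about 8.9%. It is wrong for 5 points above that rate: about 77% at 10% usual care and 73% at 12%, a shortfall of up to about 7 percentage points from 80%. The result rests only on the article's own inputs and on full outcome ascertainment from the health record. No standard formula tried, nor the stratified test, brings 12% v 17% back to 80%.

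It should not be read as showing that the power claim fails throughout or that the trial is too small for the effects it anticipates. The article allows for intervention rates up to 35%, and at 12% usual care any difference of 5.6 points or more has at least 80% power.

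**What to change.** Keep the 1000 patients and replace the single power figure with figures tied to pairs of rates, for example:

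> With 500 per arm at one-sided 0.05, power for a 5-point difference is 91% at 5% usual care, falls to 80% at about 8.9% and is 73% at 12%. At 12% usual care, power is about 85% for 6 points and 92% for 7, and the difference detectable with 80% power is 5.6 points.

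If the intended calculation paired 5% v 10% with 12% v 19%, say so and give 91% and 92%, together with the 73% for 12% v 17%, so that a reader does not carry the claim over to that case.

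The cost is a change of wording and a slightly less favourable statement for the smallest difference. No extra patients are needed, and the test, significance level and conduct stay as they are.

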#### Implementation evaluation analyses

For the hybrid evaluation of implementation process, we will use deductive analysis to explore contextual domain themes. All interviews will be audiotaped, transcribed, and checked for accuracy. A codebook with definitions will be developed using an iterative process and reviewed for face validity by experts independent of the research team. Two research staff will review and code each transcript independently using the coding framework to assess themes within each of the domains of interest (intervention and implementer characteristics, outer setting, inner setting). Coding discrepancies will be reconciled by team consensus. We will summarize survey data using descriptive statistics, including frequencies for overall scores for acceptability and appropriateness. Based on our prior experiences, we anticipate survey response rates of 50–60%, which will allow us to estimate the proportion who agree with any one survey item to within +/- 7% for these descriptive and exploratory analyses.

## Discussion

We described a protocol for a type 1 hybrid effectiveness-implementation trial to assess the impact of a digital outreach platform, mPATH^®^-CRC, on CRC screening completion among patients and process, acceptability, and sustainability measures among clinical providers and staff. Although prior studies have shown the effectiveness of the component strategies of our proposed research (text/electronic reminders, decision aids, mailed FIT) [7, 38, 39], the planned study will examine their effectiveness as a novel bundled package using a digital platform that aims to improve implementation support for low-resource settings that serve racially and ethnically diverse populations. Our study will fill critical research gaps about patient level interventions combined with clinic level implementation strategies and has potential to improve CRC screening rates among populations that continue to lag behind national increases.

As with any study, we anticipate encountering challenges common to pragmatic research with patients with limited resources. Although prior studies have shown the effectiveness of text-based reminders for CRC screening [38, 40], our study uniquely uses text messaging to engage patients in education and “self-ordering” a test. We have evidence that the digital divide is shrinking [41] and many of the patients in our study will have appropriate technology and willingness to engage, but this may be a challenge especially as communication overload and messaging fatigue is becoming more of a concern [42]. As such, the intervention will be branded by the FQHC (to improve trust) and we planned alternative strategies to reach patients without cell phones (via mail) or who fail to respond (default mailed FIT). Our study will carefully collect data on characteristics of patients to improve understanding of who is most likely to engage with the mPATH^®^-CRC platform as well as the modalities of screening preferred and completed. This data will be useful for future adaptations to the multi-component strategies and may present opportunities for more personalized messaging.

We also anticipate challenges at the clinic level. As with many low-resource settings, we expect staff turnover [43, 44] and the willingness and acceptance of clinical staff to adopt innovations in technology [45–47] to be specific challenges. Our implementation evaluation will be important to better understand these challenges in greater detail to inform future implementation strategies.

In summary, the proposed study has considerable potential to improve knowledge about effectiveness and implementation of multi-component CRC screening interventions in FQHCs and similar settings. We anticipate using the knowledge gained to inform future iterations of the multi-component strategies. For example, potentially using the technology-based platform to improve tailoring of messaging and outreach based on key demographics or screening indicators. Furthermore, we anticipate generating more robust implementation strategies that can be tested in type 2 or 3 hybrid effectiveness-implementation trials with a greater emphasis on implementation. Finally, we intend to disseminate these findings both locally (to help the FQHC adapt and sustain the intervention) as well as nationally through publications in peer-reviewed journals and scientific meetings to improve use of our lessons learned and improve CRC screening among diverse populations in a variety of contexts.

## Contributions to the literature

This paper describes a digital health platform, mPATH-CRC^®^, that serves as both an implementation and a patient-centered strategy to increase colorectal cancer (CRC) screening by automaking tasks for clinics while expanding culturally-sensitive patient outreach and education.In partnership with a rural federally qualified health center, this study will evaluate the impact of mPATH-CRC^®^ on CRC screening outcomes, while collecting quantitative and qualitative data on the integration of mPATH^®^-CRC into clinical workflows and sustainability challenges.The study results will provide new knowledge about how to use digital health strategies to optimize patient outreach and education while providing a scalable implementation strategy.

## Data Availability

No datasets were generated or analysed during the current study.
